### UGT1A1 gene testing

UGT1A1 gene testing will be performed by a single, external, biology laboratory (Beijing Ruibo Xingke Biotechnology Co. Ltd., Beijing, China). At least 2.5 mL of peripheral venous blood will be obtained from each eligible participant using a 4-mL EDTA anticoagulant blood collection tube. The blood sample will be stored and transported at − 20 °C. Genomic DNA will be extracted from each blood sample and UGT1A1*28 genotypes will be amplified by polymerase chain reaction (PCR). Gene polymorphisms will be detected using direct sequencing.

### Randomization and blinding

The relative risk of irinotecan-induced diarrhea for different UGT1A1 gene polymorphisms is wild type (TA6/6) < heterozygous mutant (TA6/7) < homozygous mutant (TA7/7). Based on this, we will perform stratified UGT1A1 genotype randomization. Eligible participants with the UGT1A1 gene will first be stratified into one of two groups - low or moderate-to-high risk of CRD - after which they will be randomized to the SXD cohort or placebo cohort for each level of risk.

Randomization will be implemented by an external agency specializing in the conduct of randomized clinical trials (Beijing Yin Rui Da Medicine Technology Co. Ltd., Beijing, China). The agency will not participate in data management or statistical analysis. Statistical Analysis System (SAS) software, version 9.4, will be utilized to stratify randomization.

The stratified ratio of participants in the low risk (TA6/6) and moderate-to-high risk (TA6/7 and TA7/7) groups will be consistent with the methods used in prior studies. In one previous study, UGT1A1 gene detection in 141 patients with cancer treated with irinotecan showed that the distribution of UGT1A1*28 TA6/6, TA6/7, and TA7/7 genotypes was 74.4% (*n* = 105), 23.4% (*n* = 33), and 2.1% (n = 3), respectively [19]. In a separate study of 2093 Chinese patients from more than 15 hospitals in Shandong, the distribution of the UGT1A1*28 TA6/6, TA6/7 and TA7/7 genotypes was 76.5% (*n* = 1601), 22.1% (*n* = 463) and 1.4% (*n* = 29), respectively [20]. The estimated stratum ratio is therefore determined to be 3:1.

The random sequence will be generated using SAS software with an allocation ratio of 1:1. SXD or placebo will be sealed in an opaque paper box labeled by randomization number and allocated based on that number. The participants will be assigned a randomization number and will receive the corresponding package, containing either SXD or the placebo.

All researchers and participants, excluding the researcher in charge of randomization, will be blinded to the assignment until the trial is completed. Emergency letters will be attached to each labeled box that will be kept by a specially assigned person in each center. If participants have severe AEs, the letters will be opened to reveal the participants’ allocated interventions.

### Intervention

All subjects will receive two cycles of irinotecan-based chemotherapy according to the 2018 National Comprehensive Cancer Network (NCCN) Clinical Practice Guideline for SCLC (version 2.0) as follows: intravenous infusion of irinotecan 65 mg/m^2^ body surface area (BSA) and cisplatin 30 mg/m^2^ on days 1 and 8, administered 3 weeks apart.

SXD and placebo will be manufactured by the pharmaceutical company New Green Science and Technology Development Co. Ltd., of Sichuan, China, according to Good Manufacturing Practices (GMP) for Pharmaceutical Products, People’s Republic of China. SXD comprises eight Chinese herbs (as shown in Table 1) that will be extracted and concentrated using a standardized Chinese formula. The resulting granules will be packed in aluminum foil bags as is permitted and regulated by the China Food and Drug Administration (CFDA). The placebo will consist of maltodextrin, starch, bitters, and food coloring, and will have a similar appearance, color, weight, taste, smell, and packaging to SXD. The participants will be instructed to dissolve their SXD or placebo and take it as a dose of 3.2 g (per bag) each time, twice daily, beginning 3 days before each cycle of chemotherapy to 11 days after the start of chemotherapy. Participants will be given antidiarrheal medication if they develop diarrhea, according to the CRD specialist consensus and guidelines [5], as detailed in Fig. 3.

**Table 1 Tab1:** Constituents of Shengjiang Xiexin decoction (SXD)

Chinese name	Botanical latin name	Proportion
Shengjiang	*Rhizoma zingiberis recens*	4
Ganjiang	*Rhizoma zingiberis*	1
Huangqin	*Radix scutellariae*	3
Huanglian	*Rhizoma coptidis*	1
Banxia	*Rhizoma pinelliae*	3
Dangshen	*Radix codonopsis*	3
Dazao	*Fructus jujubae*	4
Gancao	*Radix glycyrrhizae*	3

**Fig. 3 Fig3:**
[figure not shown]
Consensus guideline for the treatment of chemotherapy-related diarrhea

### Outcome measurement

#### Primary outcome

The primary outcome measure is the incidence and percentage of CRD in each group. CRD is defined as diarrhea occurring > 24 h after irinotecan administration and up to the completion of both chemotherapy cycles.

#### Secondary outcomes

Secondary outcomes include the degree of diarrhea, degree of neutropenia, incidence of chemotherapy regimen alterations, amount and dose of antidiarrheal drugs taken, incidence of hospitalization for diarrhea, and evaluation of chemotherapy efficacy.

Each participant will be supplied with a diary in which they will be instructed to record the time, duration, and coexisting symptoms of diarrhea. The information will then be reported to the researchers. The grade of diarrhea will be assessed for each chemotherapy cycle, and the most serious grade for each participant will be recorded to compare the difference in grades between the SXD and placebo cohorts. The diarrhea grading criteria used will be in compliance with the Common Terminology Criteria for Adverse Events (CTCAE), Version 5.0, released by the National Cancer Institute (NCI), which is detailed in Table 2. In addition, to completely evaluate each episode of diarrhea, participants will be instructed to record in detail the duration of diarrhea and the presence of coexisting symptoms, such as stomachache, abdominal distension, and cramps.

**Table 2 Tab2:** Diarrhea grading criteria

Grade of diarrhea	Definition
**Grade 1**	Increase of < 4 stools per day from baseline; mild increase in ostomy output compared to baseline
**Grade 2**	Increase of 4–6 stools per day from baseline; moderate increase in ostomy output compared to baseline; limiting instrumental ADL
**Grade 3**	Increase of ≥ 7 stools per day from baseline; hospitalization indicated; severe increase in ostomy output compared to baseline; limited self-care in ADL
**Grade 4**	Life-threatening consequences; urgent intervention indicated
**Grade 5**	Death

*ADL* activities of daily living

The development of diarrhea can affect the chemotherapy dose, duration, and schedule. Therefore, alterations in the chemotherapy schedule will be calculated in each group, including dose reductions, treatment postponement or termination, and other alterations in the preplanned chemotherapy regimen. If serious diarrhea occurs, antidiarrheal drugs and even hospitalization may be required, as determined by the recommended guidelines and expert consensus. The amounts and doses of antidiarrheal drugs prescribed and the incidence of hospitalization will be recorded. Common antidiarrheal drugs are loperamide and berberine hydrochloride [21, 22].

We will also evaluate whether SXD affects the efficacy of chemotherapy. When enrolling in the trial, eligible patients will complete the following baseline examinations: blood tumor markers (neuron-specific enolase (NSE) and pro-gastrin-releasing peptide (Pro-GRP)), chest computed tomography (CT), abdominal ultrasound, head magnetic resonance imaging (MRI), and a bone scan. After two cycles of chemotherapy, these examinations will be performed again and the Response Evaluation Criteria in Solid Tumors (RECIST1.1) will be used to evaluate the result.

Safety outcomes

The safety outcomes include AEs related to chemotherapy and SXD. Hematologic toxicity is a common AE related to the administration of irinotecan plus cisplatin [23]. Therefore, routine blood tests, including quantification of leukocytes, neutrophils, hemoglobin, and blood platelets, will be carried out before and after the day of the chemotherapy infusion (days 1 and 8 in a 21-day cycle). In addition, hepatic and renal function, blood clotting function, and electrocardiograms will be recorded at the same time. If the results are obviously abnormal, or if other severe chemotherapy-related adverse reactions occur, the chemotherapy schedule will be modified as required.

If any serious AEs related to SXD administration occur during the trial, the investigator will immediately provide the necessary diagnosis and treatment, and will report each incident to the study principal investigator within 24 h. All AEs will be surveyed and recorded in detail by an independent clinical research associate (CRA) until the participants recover to a stable condition.

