### Statistical analysis

The study data will be managed and analyzed by an independent biostatistician using SPSS (Statistic Package for Social Science, v20.0). This study includes four data sets for analysis: intention to treat (ITT), per-protocol set (PPS), full analysis set (FAS), and safety set (SS).

ITT analysis will be used to analyze the primary outcome for SXD efficacy in preventing or reducing the incidence and severity of CRD, and will include all study participants. Any missing primary outcome data will be supplemented by carrying forward the last recorded data.

PPS analysis will be performed to test the robustness of the ITT analysis and will only include participants who strictly follow the protocol and finish the study. The results from the two analyses will be considered credible if they are consistent; otherwise, the results will require sufficient discussion and explanation. Furthermore, is compliance is too low, CACE analysis will be implemented to provide an unbiased and robust estimation of treatment effect. The analysis of secondary outcomes will be based on the results of the PPS analysis.

The FAS analysis will include all randomized participants who completed at least one treatment and one follow up. To analyze the intervention-related AEs, the SS analysis will evaluate all safety outcomes for every randomized participant who received any intervention at least once during the study period.

Continuous data will be presented as the mean and standard deviation (SD), and noncontinuous data (including categorical or ranked data) will be presented as count and number (percentage). We will analyze categorical data as the risk ratio (RR) with 95% confidence intervals (CI), and analyze continuous data as mean differences (MD) and their 95% CI.

The incidence of diarrhea, modification rate of the chemotherapy regimen, and incidence of hospitalization are categorical data. The chi-square test or Fisher’s exact test will be conducted to compare the differences in those data between two groups. The Wilcoxon rank sum test will be conducted to evaluate the difference in ranked data between the two groups, which includes the grade of diarrhea and evaluation of chemotherapy efficacy. Repeated-measures analysis of variance (ANOVA) will be used to compare continuous values such as the use of antidiarrheal drugs. In all tests, a *P* value of < 0.05 will be considered statistically significant.

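### The chemotherapy-alteration outcome is justified by diarrhea, but its definition is not restricted by cause and one undivided rate is compared, so it cannot show whether any difference comes from diarrhea

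*Protocol article*

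**What the plan says.** Under Secondary outcomes, the protocol article gives one reason for measuring chemotherapy alterations: "The development of diarrhea can affect the chemotherapy dose, duration, and schedule". The alterations to be counted follow directly: "including dose reductions, treatment postponement or termination, and other alterations in the preplanned chemotherapy regimen". No cause is attached to them. In the list that opens the section, the neighbouring items read "incidence of chemotherapy regimen alterations, amount and dose of antidiarrheal drugs taken, incidence of hospitalization for diarrhea", so a cause is attached to hospitalization but not to regimen alterations.

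The Safety outcomes text names other routes to the same event. It states that "Hematologic toxicity is a common AE related to the administration of irinotecan plus cisplatin". It then lists blood counts, hepatic and renal function, clotting and electrocardiograms, and continues: "If the results are obviously abnormal, or if other severe chemotherapy-related adverse reactions occur, the chemotherapy schedule will be modified as required".

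The Statistical analysis section treats the outcome as one binary variable: "The incidence of diarrhea, modification rate of the chemotherapy regimen, and incidence of hospitalization are categorical data". The comparison is by chi-square or Fisher's exact test, without a split by reason. The same section bases the secondary outcomes on the per-protocol set, limited to participants who adhere strictly and finish. Subject withdrawal criteria ends participation when severe reactions to chemotherapy make a schedule change necessary.

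**The concern.** The question posed is whether preventing diarrhea protects the delivery of chemotherapy. The variable defined answers a wider one: whether chemotherapy was altered at all. A postponement for a low neutrophil count scores the same as a postponement for diarrhea.

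Two readings of the result are then at risk. If the other reasons act about equally in both arms, a real reduction in diarrhea-driven changes looks smaller than it is. If SXD changes other toxicity, a difference, or the lack of one, cannot be traced to its source. The second possibility cannot be dismissed from the article itself: its Background reports that SXD altered irinotecan pharmacokinetics in animals, and the degree of neutropenia is a secondary outcome in its own right.

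**Working it through.** **Plan's own figure.** There is none to reproduce. The article gives no expected alteration rate, overall or by cause, so every rate below is an assumption.

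**Model.** Let d be the probability in an arm of an alteration driven by diarrhea, and q the probability of an alteration for another reason, independent of d and equal in both arms. Then:

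- rate for any reason = 1 − (1 − d)(1 − q)
- risk difference for any reason = (1 − q) × (d on placebo − d on SXD)

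The risk difference therefore shrinks by the factor (1 − q) whatever the values of d, and the risk ratio moves toward 1.

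**Numbers.** Assume d = 15% on placebo and 5% on SXD, a risk difference of 10 points and a risk ratio of 0.05/0.15 = 0.33.

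| q | Placebo | SXD | Risk difference | Risk ratio |
|---|---|---|---|---|
| 0 | 15.0% | 5.0% | 10 points | 0.33 |
| 20% | 1 − 0.85×0.80 = 32.0% | 1 − 0.95×0.80 = 24.0% | 8 points | 0.75 |
| 30% | 1 − 0.85×0.70 = 40.5% | 1 − 0.95×0.70 = 33.5% | 7 points | 0.83 |
| 40% | 1 − 0.85×0.60 = 49.0% | 1 − 0.95×0.60 = 43.0% | 6 points | 0.88 |

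**Power.** By the normal approximation, two-sided 5%, 50 per arm, power is 38% with q = 0 and 14%, 11% and 9% with q = 20%, 30% and 40%. With larger assumed rates, 30% against 15%, it is 43% with q = 0 and 23% with q = 20%. Power is low even before dilution.

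**If other toxicity differs between arms.** Take q = 30% on placebo, so the placebo rate is 40.5%. The SXD rate equals it when (1 − 0.05)(1 − q) = 0.595, that is q = 1 − 0.595/0.95 = 37.4%. A rise of about 7 points in other-cause alterations would cancel a fall of 10 points in diarrhea-driven ones, and the pooled rate would show no difference. This is an illustration, not a prediction.

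**Who is counted.** Three statements bear on this: the outcome counts schedule changes; the withdrawal criteria end participation when severe reactions require one; the secondary outcomes use only those who finish. Read together, a patient altered for a severe reaction, whether diarrhea or hematologic, may leave the analysis because of the event being counted. The article does not allow the number to be estimated.

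**The case against.** Four arguments stand on the other side.

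*The definition never says any cause.* True. It is the plain reading of an unrestricted definition, and since the diarrhea rationale comes immediately before it, a reader could take diarrhea-related alterations as intended. The hospitalization contrast does not settle this, because the qualifier "incidence of hospitalization for diarrhea" is itself dropped in the Abstract and in Statistical analysis. What remains is that the stated definition and test do not separate causes.

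*An all-cause rate is legitimate.* It needs no attribution and shows the net effect on chemotherapy delivery, which matters in a trial that also asks whether SXD affects chemotherapy efficacy. In the cancellation example, a diarrhea-only rate would look favourable although chemotherapy had not been spared. This is a good reason not to replace the all-cause rate.

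*The illustration is fragile.* The rates are assumed, and independence is doubtful because the Discussion links UGT1A1 to both diarrhea and neutropenia. The risk ratio moves a good deal, but the risk difference loses only 2 to 4 points.

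*Reason codes may sit in the full protocol or case report form.* They may, and their absence from an article is no fault. The point concerns the outcome and test that the article does state.

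Two stronger readings are tempting and not supported. A reader might infer that changes for poor tumor response inflate the count, since Quality control lets the oncologists who judge response modify regimens. But the response examinations are repeated only after the two cycles that make up the trial, so changes based on them would ordinarily fall outside the count. A reader might also infer that the outcome hides any benefit, or that every alteration enters the count. The first exceeds what the risk differences show, and the second is contradicted by the withdrawal rule and the per-protocol analysis.

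**Conclusion.** The point holds as a mismatch between the reason given for the outcome and what its definition and analysis can show. The direction, toward no effect, follows if alterations for other reasons are independent of diarrhea-driven ones and similar in both arms. The size cannot be computed from the article; the loss of 2 to 4 points out of 10 rests wholly on the assumed rates. If SXD changes other toxicity, the direction is open, and the pooled rate cannot explain itself.

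The point is minor. It concerns one of several secondary outcomes, leaves the primary outcome untouched, and would not make this comparison conclusive at 100 patients.

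**What to change.** Keep the all-cause alteration rate as the stated secondary outcome and say explicitly that it covers any cause. For each alteration, record the main reason before unblinding: diarrhea, hematologic, other toxicity, or other. Report the diarrhea-attributed rate beside the all-cause rate, with the breakdown by reason in each arm.

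Reconcile the withdrawal criterion on schedule modification and the per-protocol basis for secondary outcomes with this outcome, so that patients who have the event are counted in its analysis.

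The cost is one field on the case report form, an added row or two in a table, and a sentence on the analysis set. The downside is small: attribution is a judgement, and the retained all-cause rate, which needs none, covers it. The reason is best recorded prospectively, because it is hard to reconstruct reliably once allocation is known.

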SXD is recorded in the traditional Chinese medicine (TCM) classic “Treatise on Febrile Diseases” from 2000 years ago. It is typically administered for the treatment of inflammatory bowel disease [14]. In our previous study, we found that SXD significantly reduced irinotecan-induced gastrointestinal toxicity, especially in the presence of the UGT1A1 mutation. It is well-known that toxicity with the mutant type is more serious than with the wild type. However, no significant differences in toxicity were noted between the mutant and the wild type when SXD was administered (*P* > 0.05) [15]. In addition, we established a model of diarrhea in the rat to explore the possible mechanisms of the antidiarrheal action of SXD. We found that treatment with SXD was associated with an inhibitory effect on intestinal apoptosis combined with a promotional effect on intestinal cell proliferation, owing to enhanced maintenance of intestinal stem cells (ISCs) [16]. Another animal study showed that SXD altered the pharmacokinetics of irinotecan and its metabolites to alleviate irinotecan-induced diarrhea, specifically by reducing the hepatic transporters multidrug resistant-associated protein-2 (Mrp-2) and P-glycoprotein (P-gp) and by upregulating UGT1A1 in the liver and jejunum [17].

We designed this study because there have been no large-scale clinical trials and little high-level clinical evidence on the treatment and prevention of CRD. The aim of our study is to evaluate the efficacy and safety of SXD prophylaxis against irinotecan-induced diarrhea in patients with SCLC, specifically that involving the UGT1A1 mutation as determined by genetic analysis before initiating chemotherapy. In this way, we hope to balance the groups by reducing the bias otherwise caused by different levels of risk of CRD in different genotypes. Meanwhile, we will also evaluate whether SXD has an impact on the efficacy of chemotherapy.

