## Discussion

Diarrhea induced by chemotherapy can affect the design and completion of chemotherapy regimens, lower the quality of life in patients with cancer, and increase medical expenses [24]. Loperamide and octreotide are currently recommended to treat CRD, as recommended by expert consensus. However, the effect of loperamide is limited [11], and there is a risk of cardiac arrhythmia when the dose and frequency are too high [12, 13]. Octreotide is not reliably effective in treating CRD. Additionally, there is currently no recommended means of preventing diarrhea. It is therefore necessary to develop an effective method of preventing or reducing the incidence of CRD that does not have significant adverse side effects. Traditional Chinese herbal medicine has recently gained more attentions for its potential to prevent or treat chemotherapy-induced adverse events [25].

Several classic TCM prescriptions have been shown to have some efficacy in treating or preventing irinotecan-induced diarrhea. For example, Banxia Xiexin decoction was shown to relieve or control diarrhea in patients with recurrent SCLC undergoing irinotecan-based chemotherapy [26]. Another Chinese herbal compound, Huangqin decoction (PHY906), was also found to reduce the incidence of irinotecan-induced diarrhea and decrease the use of loperamide [27]. In one of our previous studies in which oral SXD was administered as adjuvant therapy, the incidence of irinotecan-induced diarrhea in patients with UGT1A1 mutation was found to be nearly equal to that of patients with the wild-type mutation [15].. This effect was more notable among patients with a UGT1A1 mutation who were considered to be at high risk of developing CRD. Therefore, for this study, we included the UGT1A1 gene as a stratified random factor to balance the study groups.

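### The effect of SXD on chemotherapy efficacy is to be analysed in a per-protocol set by a Wilcoxon P value, with no effect estimate or confidence interval named; the lead analysis should use randomised patients and an interval

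*Protocol article*

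**What the plan says.** The Background closes its statement of aims with "Meanwhile, we will also evaluate whether SXD has an impact on the efficacy of chemotherapy". Secondary outcomes repeats the intention, "We will also evaluate whether SXD affects the efficacy of chemotherapy", and gives the measure: baseline examinations are repeated after two cycles and "the Response Evaluation Criteria in Solid Tumors (RECIST1.1) will be used to evaluate the result".

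Statistical analysis then fixes four things.

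- **Test.** The Wilcoxon rank sum test is for ranked data, "which includes the grade of diarrhea and evaluation of chemotherapy efficacy".
- **Criterion.** In every test a P "value of < 0.05 will be considered statistically significant".
- **Analysis set.** "The analysis of secondary outcomes will be based on the results of the PPS analysis". The PPS is limited to participants who adhered strictly and completed the study.
- **Estimates.** Categorical data get a risk ratio with 95% CI, and continuous data a mean difference with 95% CI. Ranked data get counts and percentages. The outcomes listed as categorical are diarrhea incidence, regimen modification and hospitalization; efficacy is not among them.

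Subject withdrawal criteria ends participation for a severe adverse event during chemotherapy, for a chemotherapy schedule that must be modified because of severe adverse reactions, and for non-compliance. Sample size rests on the incidence of diarrhea alone.

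**The concern.** There are two separate weaknesses.

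The first is the analysis set. Patients drop out of the PPS because of events after randomisation, and these are events that SXD is intended to influence. Secondary outcomes itself says that diarrhea can affect the dose, duration and schedule of chemotherapy. If SXD prevents severe diarrhea, the two arms lose different kinds and numbers of patients, and those who remain are no longer comparable by randomisation. The patients removed are also among those whose tumour response is most likely to be affected by altered treatment.

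The second is the form of the answer. Whether SXD affects efficacy is a question of how large a change in response the data allow. A rank test supplies a P value but no bound on that change, and in a trial of this size the bound is wide. A reader given only a non-significant P value could take more reassurance from it than the data support, on a point the trial names as an aim.

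**Working it through.** **The plan's own figures.** The article gives no response rate, margin or power statement for chemotherapy efficacy, so there is no efficacy figure to reproduce. The only size figures are those for diarrhea: about 40 evaluable per group, then 40/(1 - 0.20) = 50 per group. The dropout step reproduces. The 40 itself does not: 37.5% against 63.4%, two-sided 5%, 80% power, gives 58 per group with the usual pooled formula. That is a separate matter. Below, 40 and 50 per arm are simply taken as the patients available.

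**Assumption.** Control objective response is taken as 50-80%. This range is not in the article.

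**Precision.** If the true rates are equal, the 95% CI half-width for a difference is 1.96 × √(2p(1 - p)/n). For p = 0.6 and n = 40, this is 1.96 × √(0.48/40) = 0.215.

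| Control response | 40 per arm | 50 per arm |
|---|---|---|
| 50% | 21.9 points | 19.6 points |
| 60% | 21.5 | 19.2 |
| 70% | 20.1 | 18.0 |
| 80% | 17.5 | 15.7 |

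As an example, suppose 24/40 respond in each arm. The difference is 0, with a 95% CI of -21.5 to +21.5 points. For the RR, the standard error of the log is √(2 × (1/24 - 1/40)) = 0.183, so the CI runs from exp(-0.358) = 0.70 to exp(0.358) = 1.43.

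Now suppose 24/40 against 18/40, an observed loss of 15 points. The test statistic is z = 0.15/√(2 × 0.525 × 0.475/40) = 0.15/0.1117 = 1.34, P about 0.18. The 95% CI is 15 ± 21.6 points, from a gain of 6.6 to a loss of 36.6. This non-significant result would be compatible with a large loss.

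**Power.** For 60% against 45% at n = 40, z = (0.15 × √40 - 1.96 × √(2 × 0.525 × 0.475))/√(0.24 + 0.2475) = (0.949 - 1.384)/0.698 = -0.62, which gives 27%. At n = 50 it is 32%. Over control rates of 50-80%:

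| True fall in response | 40 per arm | 50 per arm |
|---|---|---|
| 10 points | 14-18% | 17-21% |
| 15 points | 27-32% | 32-39% |
| 20 points | 43-50% | 52-59% |

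A fall of about 30 points (29.5 to 31) is needed for 80% power at 40 per arm, and about 27 to 28 (26.5 to 28) at 50.

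**Does the Wilcoxon test do better?** It was simulated on four RECIST categories under proportional odds, with control response 50-70%, 40 per arm and 3,000 runs per scenario. Power was about 16-17%, 30-31% and 48-54% for falls of 10, 15 and 20 points. Another assumed split of the categories gave 24% for a 15-point fall. Using the full ordering changes little.

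**Selection.** Its size cannot be calculated, because the article gives no expected number of withdrawals by arm. Its direction is also open. Losing patients with modified chemotherapy could hide a harm or a benefit of SXD, depending on which arm loses more and how those patients would have responded.

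**The case against.** A Wilcoxon test is a standard choice for ordered RECIST categories, and dichotomising response discards some information. That stands, and is why the test should be kept. Counts and percentages will be shown, so a reader could work out an interval. The markers NSE and Pro-GRP are repeated after two cycles and, if analysed as continuous, would get a mean difference with 95% CI. Both points are fair. Still, the article names no interval for tumour response, and one worked out by the reader would rest on the PPS.

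Low power on a secondary outcome is not an error, and the article claims none for efficacy. That also stands; no larger trial is asked for. The aim is worded without direction, and no equivalence or preserved-efficacy claim is planned.

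Handling of missing scans can be left to an analysis plan. But the article itself fixes the test, the threshold and the analysis set, so these are open to comment.

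A reader might infer that the team already equates P > 0.05 with equality. The Background reports that "no significant differences in toxicity were noted between the mutant and the wild type when SXD was administered", while the Discussion says that the incidence of diarrhea in mutation carriers "was found to be nearly equal to that of patients with the wild-type mutation". The documents do not support that inference. One statement concerns toxicity and the other diarrhea incidence. Both cite a study that is not at hand, and its observed rates may have been close.

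A reader might also infer that every patient with modified chemotherapy leaves the PPS. The withdrawal rule covers modifications made because of severe reactions, and regimen alterations are themselves a secondary outcome.

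**Conclusion.** The concern holds in this form: an aim of the trial is to be answered in a set selected after randomisation on events that SXD is meant to change, by a P value with no effect estimate or interval named. The selection may bias the comparison in either direction, by an amount that cannot be derived from the article. A non-significant test alone would leave losses of roughly 16 to 22 points unexcluded even with equal observed response. This assumes 40 to 50 patients per arm and a control response of 50-80%; the conclusion does not turn on where in that range the rate lies.

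It would go too far to say that the trial cannot detect any effect on efficacy, since a loss near 30 points would probably be seen. It would also go too far to say that the article plans to read a non-significant result as no effect. It says nothing of the kind; it only lacks a statement that prevents it. The change should be made, but the primary analysis does not depend on it.

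**What to change.** For chemotherapy efficacy, specify the following.

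1. **Lead analysis set:** all randomised patients who start chemotherapy, in the arm to which they were allocated.
2. **Estimate:** objective response by RECIST 1.1, as a risk difference and RR with 95% CI. Patients without an evaluable scan count as non-responders.
3. **Alongside it:** the Wilcoxon test on the RECIST categories.
4. **Supportive:** the same analyses in the PPS.
5. **Reading:** the conclusion rests on the interval and states the largest loss of response not excluded. P > 0.05 will not be taken as evidence that SXD leaves efficacy unchanged.

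The cost is analysis wording, using examinations already planned. There are two drawbacks. The trial could not claim preserved chemotherapy efficacy from a non-significant test. Counting unevaluable patients as non-responders is conservative for the response rates, and since participation can end before the scan after two cycles, an arm with more withdrawals will show a lower rate for that reason. The number of unevaluable patients per arm should therefore be reported next to the result.
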